## Abstract

**Methods::**

This will be a blind, randomized, and controlled clinical trial, which will be carried out on children between 6 and 12 years of age who enter the Catholic University of Uruguay, Faculty of Health Sciences, Postgraduate School, for treatment. To be included, children must present temporomandibular disorders, based on the diagnostic criteria will be the Research Diagnostic Criteria for Temporomandibular Disorders (RDC/TMD). Forty-five participants will be randomized to three groups: Group 1—ILIB with 2 sessions of 20 minutes for 12 weeks (n = 15); Group 2—Placebo laser application with 2 sessions of 20 minutes for 12 weeks (n = 15); Group 3—Control with no treatment (n = 15). Irradiation will be performed by continuous and direct transcutaneous application to the radial artery, by means of a bracelet that inserts the laser beam. The laser to be used is infrared, power 100 mW ± 20%, wavelength 808 nm ± 10 nm, continuous application. RDC/TMD and pain evaluated through a visual analog scale will be the outcome measures.

**Discussion::**

Due to the low level of evidence, new studies are needed on the effect of ILIB in children with TMD.

## 1. Introduction

The American Dental Association has adopted the term temporomandibular disorder (TMD) to refer to all functional disturbances of the masticatory system.^[1]^ They represent a heterogeneous group of pathologies that affect the temporomandibular joint (TMJ), the masticatory muscles, or both, characterized by signs such as muscle and/or TMJ pain, TMJ sounds, and restriction or deviation of the opening trajectory from the mouth. The Research Diagnostic Criteria for Temporomandibular Disorders (RDC/TMD) is the reference standard among classification systems in this field of research.^[2]^ Many children diagnosed with TMD have adaptive physiological changes during growth and development, but if the diagnosis is late, already in an adult stage, it can become irreversible.

Low intensity laser therapy, or photobiomodulation (PBM), is capable of inducing a photobiological response within cells. The use of red and infrared light stimulates repair, relieves pain and reduces inflammation. The primary chromophores are identified as cytochrome c oxidase in mitochondria and calcium ion channels. Secondary effects of photon absorption include increases in ATP, in reactive oxygen species (ROS), in nitric oxide, and modulation of calcium levels. There is a dose regimen whereby low light levels have stimulating effects, while high light levels have inhibitory effects. Photobiomodulation is capable of upregulating antioxidant defenses and reducing oxidative stress. One of the most reproducible effects of photobiomodulation is an overall reduction in inflammation, which is particularly important for joint disorders.^[3]^

The most commonly used light sources for photobiomodulation are lasers (light amplification by stimulated emission of radiation) and LEDs (light-emitting diodes). Red phototherapy activates cell signaling pathways that modulate cell function. This light source is economical, consumable, portable, easy to operate, and can be combined with other treatments. It increases adenosine triphosphate (ATP),^[4,5]^ achieving a hemodynamic response of coupled oxygen delivery and blood volume,^[6]^ inducing positive effects on immunoglobulins, interferons and interleukins.^[4]^

Photobiomodulation regulates antioxidant defenses and reduces oxidative stress. The micro and macrovascular response accompanies the evidence shown by the systemic effects of intravascular laser irradiation of blood (ILIB).^[7]^ One of the most reproducible effects of photobiomodulation is an overall reduction in inflammation. It is also used to accelerate wound healing, collagen production, and modulation of the immune system.^[4,6]^ These characteristics are due to monochromaticity, the main property of laser light, that is, an extremely narrow spectral area (line), which makes it much easier to define and control the energy of laser light, besides being non invasive, low cost and safe.^[8,9]^

Therefore, the aim of this study is to verify if the use of intravascular laser irradiation of blood (ILIB) influences the reduction of pain and increases the range of motion in opening and closing in children and adolescents with TMD.

## 2. Methods

### 2.1. Study registration

This is the first version of a protocol that was registered in ClinicalTrials.gov, under the registration number: NCT05297604, first posted on 28 March, 2022 and last updated on 31 August, 2022. Available online at: https://clinicaltrials.gov/ct2/show/NCT05297604.

### 2.2. Type of study

This study is a protocol for a randomized, paralell group, blinded, controlled clinical trial. It is described according to the criteria established in the Standard Protocol Items: Reccomendations for Interventional Trials (SPIRIT) statement and Figure 1 is the SPIRIT figure.

**Figure 1. F1:**
[figure not shown]
SPIRIT figure as recommended by 2013 SPIRIT statement. SPIRIT = Standard Protocol Items: Reccomendations for Interventional Trials.

### 2.3. Ethics committee

The study will follow the regulatory standards for research in human beings of the Research Ethics Committee of the Catholic University of Uruguay, under the process number 220824b. Participants must sign a written informed consent form after all aspects related to participation in the research have been clarified, in accordance with Decree No. 158/019, in force in the Eastern Republic of Uruguay. The children and adolescents will also sign an assent form. One of the researchers responsible for the procedures will explain the consente forms. The study will be carried out in accordance with the Declaration of Helsinki. The study participants will be recruited and treated at the Dental Diagnostic Clinic of the University Health Clinic, Graduate School of the Catholic University of Uruguay, from September 20, 2022 to May 20, 2023.

### 2.4. Participants

The study will include children between 6 and 12 years of age who enter the Catholic University of Uruguay, Faculty of Health Sciences, Postgraduate School, for treatment. Patients will already be in treatment for other conditions at the clinic, what will facilitate recruitment. It is believed that the need for treatment of TMD before major pain sympthoms will help to improve adherence to the trial.

#### 2.4.1. Inclusion criteria.

Healthy participants;Children and adolescents diagnosed with TMD;From 6 to 12 years old;Have a complete dentition (except third molars);Present deviation and/or mandibular deflection.

#### 2.4.2. Exclusion criteria.

Patients with craniofacial anomalies, genetic syndromes since this is due to the fact that people with anomalies of this type are more likely to suffer from TMD due to other factors associated with their malformation, which would be a confounding variable for this study.Patients presenting occlusal changes; make use of any type of dental prosthesis; be undergoing orthodontic treatment or need orthognathic surgery or physical therapy; since it would alter the results of both diagnosis and treatment.Patients undergoing cancer treatment: because it is necessary that patients do not have any condition that alters their general health, since this may cause a different response to the proposed treatment.Patients who start using any type of medication during any phase of the study because it may cause a different response to the proposed treatment.Patients with photosensitivity since it will not be possible to apply part of the treatment.

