#### 2.5.2. Pain evaluation.

This is the secondary outcome of the study and it will be assessed at baseline and after the 12 weeks of treatment. Pain will be evaluated using a visual analog scale (VAS). It is a subjective scale to measure the intensity of pain, described by the patient. The child is asked to mark the intensity of the pain on a corresponding linear scale from 0 to 10, taking 0 without pain and 10 extreme pain. The point indicated by the patient is the intensity.^[10,12]^

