### 2.7. Interventions

#### 2.7.1. ILIB therapy protocol.

Participants will receive the ILIB treatment for 20 minutes. The laser to be used is infrared-red, with power of 100 mW ± 20%, wavelength 808 nm ± 10 nm, continuous application.^[13]^ These parameters were taken as a reference since they were presented in a previous article, in which it was considered safe and did not cause discomfort to the patients. The technique is not invasive, the point of irradiation is by continuous and direct transcutaneous application to the radial artery by means of a bracelet that inserts the laser beam. Two sessions of 20 minutes will be conducted per week, for 12 weeks.

Study participants will undergo 2 phases of collection. The first, called the Control Phase, in which the individuals are evaluated, and will remain for a week without any physical and/or dental intervention, followed by a new evaluation and the start of the second phase, called the Treatment Phase, in which individuals will be assigned to one of three research groups.

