#### 2.7.2. Groups.

•Group 1 ILIB (n = 15): Participants will be subjected to ILIB protocol sessions. It is a noninvasive technique that consists of a low-intensity laser that is attached to a bracelet that has been developed so that the light beam is transported transcutaneously over the radial artery.^[12]^ They will receive 2 sessions per week for 12 weeks, and will be reassessed 1 month after the end of the proposed therapy.•Placebo Group (n = 15): Participants will be treated in the same way as the ILIB group. The person in charge of the ILIB application will simulate the irradiation with the equipment kept off. So that the participant does not identify the group to which he/she/they belong, the device activation sound (beep) will be turned on at the time of application. They will receive 2 sessions per week for 12 consecutive weeks.•Control Group (n = 15): Composed of individuals who will not receive any type of intervention. Before the procedure and 1 month after the end of therapy, pain will be assessed using the VAS and the opening and closing movement will be measured with a digital caliper.

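### The medication exclusion in 2.4.2 reaches past randomisation, so it can remove randomised children for a reason linked to pain and can bias the group comparison

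*Protocol article*

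**What the plan says.** Section 2.4.2 lists as an exclusion "Patients who start using any type of medication during any phase of the study". The reason given there is that medication may change how a child responds to the treatment.

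Section 2.7.1 defines the phases: "Study participants will undergo 2 phases of collection". The first is a Control Phase week without intervention. The second is "called the Treatment Phase, in which individuals will be assigned to one of three research groups".

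Section 2.7.2 sets the length of the period after assignment; for the ILIB group it says "They will receive 2 sessions per week for 12 weeks, and will be reassessed 1 month after the end of the proposed therapy". It describes the third group as "Composed of individuals who will not receive any type of intervention". The placebo group receives a switched-off device with the activation beep.

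On pain measured by VAS, section 2.5.2 says "This is the secondary outcome of the study and it will be assessed at baseline and after the 12 weeks of treatment". The primary outcome, RDC/TMD (section 2.5.1), also reflects pain-related features. On the setting, section 2.4 says "Patients will already be in treatment for other conditions at the clinic".

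Section 2.10 allows for 10% loss from 45 children. Section 2.11 expects no more than 5%. No section limits the medication rule to the time before assignment, or says that a child who meets it later stays in follow-up or in the analysis.

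**The concern.** An eligibility criterion can only act on what is known before randomisation. Starting a drug in the Treatment Phase happens afterwards, so this rule removes children who already belong to a randomised group.

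The event need not be neutral. Any type of medication includes analgesics and anti-inflammatories, whose use can follow pain. Pain is the VAS outcome and enters RDC/TMD. The article's own reason for the rule is that medication may change the response. If starts also differ by arm, because ILIB relieves pain or because families who know the child is untreated turn to drugs sooner, the children who remain are no longer comparable between arms.

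Two things are at stake: a selection bias that randomisation no longer protects against, and avoidable loss from groups of 15. If outcomes are not collected after removal, no later analysis can restore them.

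**Working it through.** **Does the rule reach past randomisation?** The rule applies in any phase (2.4.2). There are two phases, and assignment belongs to the second (2.7.1). So it covers at least the 12 treatment weeks. Whether it also covers the month to the later reassessment is not stated.

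**The article's own loss figures.** 15 × 0.10 = 1.5 per group, as section 2.10 states, or 4.5 of 45. The 5% in section 2.11 is 45 × 0.05 = 2.25 children. The total of 45 cannot be rebuilt, because no effect size, SD or power is given; nothing below depends on it.

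**Bias under sharp selection (shares assumed).** If the worst share p of a normal outcome is removed, the mean of the rest shifts by −φ(z)/(1 − p) SD, where z cuts off the upper share p.
- p = 0.20: −0.280/0.80 = −0.350 SD
- p = 0.10: −0.1755/0.90 = −0.195 SD
- p = 0.05: −0.1031/0.95 = −0.109 SD

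| Comparator removed | ILIB removed | Shift in the contrast |
|---|---|---|
| 20% | 5% | 0.350 − 0.109 = 0.241 SD against ILIB |
| 10% | 5% | 0.195 − 0.109 = 0.086 SD against ILIB |
| equal share | equal share | 0 |
| 5% | 20% | 0.241 SD in favour of ILIB |

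With an assumed VAS SD of 2, 0.241 SD is 0.241 × 2 = 0.48 points.

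**Bias under graded selection (simulated, all inputs assumed).** Final VAS had mean 4 and SD 2 in the comparator arm and was held within 0 to 10. The chance of starting a drug was logistic in pain, with slope 1 per point and midpoint 5 to 7. Medication itself was assumed not to change VAS.

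| Scenario | Difference, all kept | Difference, starters removed | Removed: comparator / ILIB |
|---|---|---|---|
| Nominal benefit 1 point | 0.96 | 0.66 to 0.80 | 13–35% / 7–22% |
| Nominal benefit 2 points | 1.85 | 1.33 to 1.60 | 13–35% / 3–13% |
| No benefit, same behaviour | 0 | 0 | equal |
| No benefit, comparator starts at 1 to 2 points less pain | 0 | 0.16 to 0.38 against ILIB | 13–22% / 3–13% |

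A real benefit shrinks by between 1 − 1.597/1.852 = 14% and 1 − 0.662/0.958 = 31%.

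**Loss of sample.** If each child starts some drug with probability q, for whatever reason, the number removed is binomial with n = 45. Three or more exceeds the 5% expectation; five or more exceeds the 10% allowance.

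| Assumed q | Mean removed per arm | P(3 or more of 45) | P(5 or more of 45) |
|---|---|---|---|
| 0.10 | 1.5 | 0.84 | 0.47 |
| 0.20 | 3.0 | 0.997 | 0.96 |
| 0.30 | 4.5 | above 0.999 | 0.999 |

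At q = 0.30, 15 − 4.5 = 10.5 per arm remain. The difference detectable with 80% power (two-sample t test, two-sided 0.05; power and sidedness are my assumptions) rises from 1.06 to 1.29 SD.

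**The case against.** The strongest reply is that the document gives no medication rates, analgesic use or VAS levels, so bias is not shown. That stands as to size and direction. A reader might infer that the rule is bound to remove children differently by arm and so does bias the pain comparison. The text does not support this: arm-dependence is an inference.

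Further limits also stand:
- Pain-driven medication may be uncommon. Section 2.4.1 asks for healthy children and requires a TMD diagnosis with deviation or deflection, not pain. Section 2.4 speaks of treating before major pain symptoms.
- Knowing that one is untreated applies only to the control group. Between ILIB and placebo, different medication use would mainly need a real ILIB effect, and in the scenarios run the bias then shrinks that effect.
- Drugs taken for unrelated conditions cost sample size but need not cause bias. That children are under other treatment makes such starts plausible; it does not show that they will be frequent.
- Keeping starters has its own consequence. If medication lowers VAS by d SD, the 20% and 5% shares shift the contrast by (0.20 − 0.05)d = 0.15d SD against ILIB, or 0.15 SD at an assumed d = 1. That belongs to an effect that includes medication use, but it is a choice to be stated.

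A last reply is that analysis sets are commonly left to a fuller document, and that exclusion might mean stopping participation rather than removal from the analysis. It is fair that section 2.11 does not say starters are dropped from the analysis, so a flat claim that the groups will not be analysed as randomised goes too far. But the point is a rule that the article states, not a detail that it leaves out. On either meaning, the rule as written takes randomised children out of the trial.

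**Conclusion.** The point holds as a risk created by a stated rule. The medication exclusion extends beyond randomisation and can remove children for an event that depends on pain and possibly on arm. It can therefore bias the comparison, most plausibly the one with the untreated group.

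The size cannot be fixed from the document. Under the assumed 20% and 5% removal the shift is about 0.24 SD against ILIB. It is zero with no effect and equal medication use, and it could run the other way if starts were more common under ILIB. The effect was worked out for pain on the VAS, the secondary outcome; RDC/TMD is exposed through its pain features, but no figure was derived for it. The loss of sample is separate: if only 10% of children start any drug, the chance of exceeding the 5% expectation is 0.84, before ordinary dropout.

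**What to change.** In section 2.4.2, apply the medication criterion as an eligibility condition only up to randomisation. In section 2.11, state that, whatever the trial's rule on medication use, every randomised child stays in follow-up and in the primary analysis in the assigned group. Record each medication start (drug, reason, dates), report starts by arm, and exclude starters only in a labelled sensitivity analysis.

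This costs about two sentences and a medication log. The downside is that the primary estimate then includes the effect of any concomitant medication, which the text should say. Which medication is permitted is a clinical matter and is not addressed here.

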### 2.5. Evaluations

#### 2.5.1. Research Diagnostic Criteria for Temporomandibular Disorders.

The Research Diagnostic Criteria for Temporomandibular Disorders (RDC/TMD) will be used to determine TMD and assess participants. This is the primary outcome of the study and it will be assessed at baseline and after the 12 weeks of treatment. This evaluation consists of a clinical examination based on a detailed physical evaluation, checking the pattern of mouth opening, vertical extension of mandibular movement, TMJ sounds on palpation for vertical extension of movement, excursive mandibular movements, TMJ palpable sounds during right and left lateral excursion and protrusion.

The clinical diagnosis with RDC/TMD is divided into 3 groups: Group I, Muscle diagnoses (myofascial pain and myofascial pain with limited opening); Group II, Disc Displacement (displacement with reduction, displacement without reduction with limited opening, and displacement without reduction, without limited opening); Group III, Arthralgia, arthritis, osteoarthritis (arthralgia, TMJ osteoarthritis and TMJ osteoarthritis). The range of mandibular movement will be determined with the help of a digital caliper.^[10,11]^

The questionnaire that forms an integral part of the RDC/TMD is made up of 31 items that involve general health, oral health, history of facial pain, opening limitation, noise, habits, biting, tinnitus, illnesses in general, joint problems, headache, behavior, current economic, and social profile.

RDC/TMD reflects the interaction between clinical criteria and disabling features related to pain and psychological status, assigning from no diagnosis to a maximum of 5 (a Group I diagnosis + a Group II diagnosis + a Group III diagnosis) for each joint.

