### 2.11. Statistical analysis

The data will be tabulated and processed using the G Power version 3.1.9.2 program. The values will be tested for normality by the Kolmogorov–Smirnov test, and will be expressed as mean and standard deviation if Gauss curve is assumed. For the comparison between the groups, the T test will be carried out, considering a level of significance of 0.5% (*P* < .05). No loses greater than 5% of the sample are expected.

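### The primary outcome is the RDC/TMD instrument with no variable fixed, its stated maximum does not add up, and the only stated test does not suit its diagnoses

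*Protocol article*

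**What the plan says.** Section 2.5.1 of the protocol article says of the RDC/TMD: "This is the primary outcome of the study and it will be assessed at baseline and after the 12 weeks of treatment". The section then describes several things under that one name:

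- a physical examination covering opening pattern, vertical and excursive movement, and joint sounds;
- a 31-item questionnaire;
- diagnoses, of which it says "The clinical diagnosis with RDC/TMD is divided into 3 groups" (muscle, disc displacement, and arthralgia or arthritis types);
- a measurement in mm: "The range of mandibular movement will be determined with the help of a digital caliper".

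The only numerical range given is a count of diagnoses, from none "to a maximum of 5 (a Group I diagnosis + a Group II diagnosis + a Group III diagnosis) for each joint".

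The Introduction states the aim as finding out whether the treatment "influences the reduction of pain and increases the range of motion in opening and closing in children and adolescents with TMD". Pain on a 0 to 10 VAS is covered in section 2.5.2: "This is the secondary outcome of the study and it will be assessed at baseline and after the 12 weeks of treatment". Section 2.7.2 places a reassessment of the ILIB group one month after treatment ends. For the control group it lists VAS and caliper movement, before the procedure and at that same later point, without mentioning diagnoses.

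Section 2.11 gives one analysis: a Kolmogorov–Smirnov check, mean and SD if normality is accepted, and then "For the comparison between the groups, the T test will be carried out".

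**The concern.** A primary outcome has to be one quantity per randomised child, at one time, that the planned test can compare. What is fixed here is an instrument. Its parts are of different types: nominal categories, a short count and a length in mm. Each leads to a different analysis, and section 2.11 describes an analysis for only one type. The single figure that might define a score contradicts the components listed beside it, so the score cannot be rebuilt from the text.

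An analyst who follows the plan as written must therefore choose the primary variable later, possibly after seeing the data. That choice carries its own false-positive risk, and it would fall on the result that supports the trial's main conclusion.

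**Working it through.** **1. The stated maximum.** Inputs, all from section 2.5.1: a stated maximum of 5 for each joint, made up of one diagnosis from each of Groups I, II and III.

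- As written, per joint: 1 + 1 + 1 = 3, not 5.
- Two joints, with the muscle diagnosis counted at each: 2 × 3 = 6 per child.
- Muscle diagnosis counted once, Groups II and III in each of two joints: 1 + 2 × (1 + 1) = 5 per child.

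The figure 5 is reproduced only by the last reading, which is per child and applies the joint qualifier to Groups II and III alone.

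**2. Which variable fits the stated analysis.** Section 2.5.1 allows three forms of the outcome; section 2.11 offers mean, SD and t test.

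| Form of the outcome | Does mean and t test fit? |
|---|---|
| Nominal diagnosis | No. Categories have no mean, and no categorical method is stated. |
| Count of diagnoses, 0 to 5 | Roughly for error rate, but the normality check may fail and no fallback is stated. |
| Caliper movement, mm | Yes. |

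The count was checked by simulating two groups of 15 (40,000 runs, two-sided 0.05). The documents give no distribution, so three were assumed for counts 0, 1, 2, 3, 4, 5. Normality was tested against the fitted normal in 2,000 samples each.

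| Assumed distribution | Type I error of t test | Kolmogorov–Smirnov rejects |
|---|---|---|
| Spread (0.10, 0.30, 0.25, 0.20, 0.10, 0.05) | 0.050 | 3% |
| Mostly one (0.05, 0.70, 0.15, 0.06, 0.03, 0.01) | 0.045 | 85% |
| None or one only (0.30, 0.70) | 0.055 | 100% |

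The t test roughly keeps its level in all three. In the last two, the plan's own check would usually or always reject normality, and section 2.11 then gives no next step.

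**3. Cost of leaving the choice open.** Inputs: level 0.05 (section 2.10); three candidate outcomes, namely diagnosis, count and mm; one contrast between two arms. If the three were independent and the most favourable one could be reported:

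1 − (1 − 0.05)³ = 1 − 0.857 = 0.143, about 14%.

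The three come from the same examination and are likely to be positively correlated, which brings the figure down towards 5%.

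**4. Aim and timing side by side.** Range of motion is named in the aim and measured within the primary-outcome section, but is not singled out. Pain is named in the aim and is secondary. Sections 2.5.1 and 2.5.2 assess after the 12 weeks; section 2.7.2 assesses a month after treatment ends. Which of these is the primary time point is not settled.

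**The case against.** The strongest defence is that this is a condensed article and that an analysis plan may name the variable. That would excuse missing detail. It does not excuse a section devoted to the primary outcome that fixes an instrument, gives a maximum its own components do not support, and is paired with a test that does not suit diagnoses.

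A second defence is that the maximum is probably misplaced wording, since one reading restores 5, and that nothing says the count is the analysed score. This stands. Taken alone, the maximum needs only a wording correction.

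Four stronger readings are tempting, and the documents do not support them:

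- *The t test cannot be used on this outcome at all.* It suits movement in mm and roughly holds its level for a 0 to 5 count. It fails only for nominal diagnoses.
- *The joint is the unit of analysis, so each child would count twice.* Section 2.10 counts participants, 15 per group, and section 2.11 compares groups. No by-joint analysis is planned.
- *The primary outcome misses the aim.* The mismatch is only partial: range of motion sits inside the primary-outcome section, and pain is the named secondary outcome.
- *The false-positive risk is well above 14%.* A larger figure needs the three pairwise arm comparisons added in. Those alone give about 0.11 to 0.13 in the same simulations, even with one fixed outcome. They are a separate matter and should not be charged to the choice of outcome.

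**Conclusion.** The point holds in this form: the primary variable is not fixed, the stated maximum does not follow from its own components (3 per joint; 5 only per child), and the sole stated analysis does not suit the diagnostic form of the outcome.

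The arithmetic on the maximum needs no assumption beyond two joints per child. The rise from 5% to about 14% rests on three candidates, independence, a single contrast and a level of 0.05; positive correlation makes it smaller. The simulated results rest on assumed count distributions and show only that the count is a borderline case. Because the gap concerns the primary outcome, it should be closed before unblinded data are seen.

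**What to change.** - Name one primary variable per child at one time point. Caliper-measured mouth opening in mm is a suitable candidate: it already belongs to the RDC/TMD examination, the aim names it, and the stated test fits it. One caution is that section 2.4.1 requires mandibular deviation and/or deflection, not limited opening, so some children may have little room to gain. The trial team should weigh this before settling on it.
- Keep VAS pain as the secondary outcome.
- Report RDC/TMD diagnoses per child as a categorical secondary outcome, for example the share of children with no diagnosis, with an exact test.
- Correct the maximum to 5 per child, stating that the muscle diagnosis counts once and Groups II and III count in each joint.
- Reconcile the assessment time in sections 2.5.1 and 2.5.2 with that in section 2.7.2, for all three groups.

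The cost is a dated amendment made before unblinded data are seen. No new kind of measurement is needed, though the caliper reading must be taken in every group at the time point chosen. The downside is that a change to the primary outcome must be documented openly. The registry entry is not part of the material reviewed, so whether it also needs changing should be checked against its content.
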